# Physiotherapy plus conventional treatment versus conventional treatment only in the treatment of functional constipation in children: design of a randomized controlled trial and cost-effectiveness study in primary care

**DOI:** 10.1186/s12887-018-1231-7

**Published:** 2018-07-31

**Keywords:** Constipation, General practitioner, Pelvic floor, Child and adolescent, Family medicine

## Abstract

**Background:**

Our aim was to design a study to evaluate the effectiveness and cost-effectiveness of adding physiotherapy to conventional treatment for children with functional constipation in primary care. Physiotherapy is focusing on improving the coordination between the pelvic floor and abdominal musculature during bowel movement, while conventional treatment is mainly focusing on symptomatic relief of symptoms, therefore, we expect the effects of physiotherapy will be more sustainable than the effects of conventional treatment. In this paper we describe the final study design and how the design was adapted, to overcome recruitment problems.

**Methods:**

We designed a randomized controlled trial of children aged 4–17 years with functional constipation diagnosed by a general practitioner or pediatrician. Children in the intervention group received physiotherapy plus conventional treatment, and those in the control group received conventional treatment only. Follow-up measurements took place at 4 and 8 months. The primary outcome was treatment success defined according to the Rome-III criteria as the absence of functional constipation, with no laxative use. Secondary outcomes were absence of functional constipation irrespective of laxative use, quality of life, global perceived effect, and costs.

Children were recruited from September 2014 to February 2017. Initially, we aimed to include children with recent symptom onset. However, in the first phase of enrollment we were confronted with an unforeseen recruitment problem: many children and their parents refused randomization because physiotherapy was considered too burdensome for the stage of disease. Therefore, we decided to also include children with a longer duration of symptoms. In total 134 children were included.

**Discussion:**

The target number of participants is achieved. Therefore, the results may change thinking about the management of functional constipation in children.

**Trail registration:**

Netherlands Trial Register (NTR4797), registered 8 September 2014.

## Background

Functional constipation (FC) is a common problem in children [1]. Its etiology is multifactorial, involving age, behavior, pelvic floor function, and gastrointestinal motility. Conventional treatment includes education, dietary advice, toilet training, and laxatives [2, 3]. However, despite this multifaceted approach, 50% of children still experience FC after 6–12 months’ treatment with laxatives and 25% have symptoms that persist into adulthood [4, 5]. Therewith FC has not only a major impact on the quality of life of both children and their families but also increases healthcare costs significantly [6–8].

The pelvic floor and abdominal muscles contract and relax in a coordinated manner during bowel movements, and dysfunction of this interaction could be important in the onset and maintenance of FC [9]. Children with FC, either consciously or unconsciously, appear to strain their pelvic floor muscles and fail to relax the external anal sphincter during bowel movements [10, 11]. In addition, reduced trunk stability may preclude achievement of the posture and intra-abdominal pressure required for defecation [10, 12]. Physiotherapy for FC focuses on improving this coordination between the abdominal and pelvic floor musculature [9]. To date, two small clinical trials in specialist care have shown promising results for the effects of physiotherapy in children with FC [13, 14]. Physiotherapy is expected to give optimal results in children with recent symptom onset [4]. Therefore, it could be particularly effective in children presenting to primary care.

We aimed to design a randomized controlled trial to evaluate the effectiveness and cost-effectiveness of physiotherapy plus conventional treatment in comparison to conventional treatment alone for children aged 4–17 years presenting with FC in primary care. We encountered problems in the recruitment of participants that led us to change the original criteria for participant selection. In this paper we therefore start with presenting our final study design. Thereafter, we describe the process of recruiting participants, including the changes implemented in the original study design. Lastly, we evaluate the representativeness of our study population by comparing characteristics of children that participated and refused to participate in this trial.

## Methods

### Design

We designed a randomized controlled trial that had a follow-up period of 8 months, and wherein children were included between September 2014 and March 2017. The trial was approved by the Medical Ethical Board of the University Medical Center of Groningen (METC2013/331) and was registered in the Netherlands Trial Register (NTR4797). Before enrollment we obtained written informed consent from all parent(s). In addition, children aged ≥12 years provided written informed consent themselves.

### Participants

#### Eligibility criteria

Children were eligible for inclusion if aged 4–17 years and diagnosed with FC by a general practitioner (GP) or general pediatrician. Specifically, children were required to have experienced FC symptoms or to have used laxatives in the 4 weeks before enrollment. Children under the age of 4 years were considered too young to undergo physiotherapy [9]. The exclusion criteria were psychopathology affecting protocol adherence, severe disease (physician determined), and physiotherapy or urotherapy for constipation in the past 3 years (Fig. 1).

**Fig. 1 Fig1:**
[figure not shown]
Flowchart of study design: eligibility criteria for participants, planned measurement and timing of baseline characteristics and the primary and secondary outcome measurements. Abbreviations: FC, functional constipation, QPGS-RIII, Questionnaire on Pediatric Gastrointestinal Symptoms Rome-III, EQ-5D-Y, EuroQol-5-dimensions-youth, iMTA, Institute of Medical Technology Assessment Medical Consumption Questionnaire, DDL, Defecation Disorder List

#### Patient recruitment

We recruited all children (aged 4–17 years) presenting to general practices or who were newly referred to pediatric outpatient departments with a diagnosis of FC. During the first consultation for FC symptoms, parents and children were informed about this study by their treating physician (incident cases). In addition, any children with a known diagnosis of FC and who had consulted their GP in the past 12 months for this diagnosis were sent a leaflet explaining the study (prevalent cases). Children or their parents (depending on the child’s age) were asked to complete a short questionnaire supplied with the leaflet, detailing whether the child had experienced symptoms of FC or used laxatives in the past 4 weeks. Once completed, they were asked to return the questionnaire.

### Interventions

#### Control group: conventional treatment only

Children in the control group received conventional treatment. No restrictions or recommendations were given to the physicians regarding treatment. However, education, dietary advice, toilet training, and when indicated, laxative prescribing were permitted based on appropriate guidance [2, 3].

#### Intervention group: physiotherapy plus conventional treatment

Children in the intervention group received physiotherapy in addition to conventional treatment. Physiotherapy consisted of a maximum of nine half-hour sessions carried out by specialist physiotherapists, and ended if the physiotherapist considered that treatment was successful or that no more improvement was expected. The physiotherapists were trained to master’s degree level in pediatric or pelvic physiotherapy, and had received postgraduate education in the treatment of bladder and bowel dysfunction in children. The patient-tailored structured treatment program used in this study was developed in cooperation with experienced specialist physiotherapists and approved by all participating specialist physiotherapists before the study. The physiotherapist tailored the treatment program to the individual patient. For each patient and session, the physiotherapists recorded on a structured form the treatment options used to reach the six goals.

In young children, physiotherapy focused on the child and his or her parent(s), while in older children, the focus was mainly on the child. All exercises, materials, and methods were presented in a manner appropriate to the child’s developmental age and locomotor skills. For the patient-tailored structured treatment program used in this study, the six goals were: 1) improving the knowledge about defecation, and the role that the child and/or parent might have in the persistence of symptoms; 2) improving toileting behavior and practicing a stable toilet posture; 3) increasing awareness of the sensation of needing to defecate; 4) learning to relax while defecating; 5) learning to breath correctly to generate adequate intra-abdominal pressure for defecation; and 6) teaching effective straining for defecation. Biofeedback and electrotherapy were not allowed in this study because there is insufficient evidence of their efficacy in children with FC and because we considered these therapies too invasive for treatment of children presenting to primary care [15].

### Randomization and blinding

Children were randomly allocated in a 1:1 ratio to the two treatment groups, using a computer-generated randomization list with random block sizes. Randomization was stratified into those aged 4–8 years and those aged 9–17 years. The randomization list was maintained by a researcher who was not involved in the study and had no access to the allocation site.

Children, parents, physicians, and physiotherapists could not be blinded to the intervention. The investigator was blinded to the assigned study group during data entry and statistical analyses.

### Outcomes

The primary outcome was treatment success, defined according to the Rome-III criteria as the absence of FC without laxative use (see Table 1 for the Rome-III criteria used to define FC) [16]. Thus, a successfully treated child was required to fulfill none or one of the six Rome-III criteria. Other secondary outcomes were absence of FC according to the Rome-III criteria irrespective of laxative use, quality of life, global perceived treatment effect, and costs.

**Table 1 Tab1:** Description of the Rome III criteria for functional constipation [16]

According to the ROME III criteria, a child must have a developmental age of at least 4 years and fulfill two or more of the following criteria, at least two months prior to diagnosis^a^:	
1) two or fewer defecations in the toilet per week,	
2) at least one episode of fecal incontinence per week,	
3) history of retentive posturing or excessive volitional stool retention at least once a week,	
4) history of painful or hard bowel movement at least once a week,	
5) presence of a large fecal mass in the rectum at least once a week,	
6) history of large diameter stools that may obstruct the toilet at least once a week.	

^a^For the purpose of this study, patients were eligible for enrollment if symptoms were present for at least one month before diagnosis, rather than two months, which is in agreement with the recently published Rome-IV criteria [27]

### Measurements

Figure 1 gives an overview of the measurement and timing of baseline characteristics and the primary and secondary outcome parameters; follow-up measurements took place after 4 and 8 months. We collected the following data at baseline: age, gender, symptom duration, age at symptom onset, symptom chronicity, and whether lower urinary tract symptoms were present. Symptom chronicity was defined as continuous or regular laxative use (≥3 periods) in the 12 months before inclusion.

#### Measurement of the primary outcome

The presence of FC was assessed with a Dutch version of the Questionnaire on Pediatric Gastrointestinal Symptoms Rome-III (QPGS-RIII) [16]. This standardized questionnaire was used to assess if children have experienced functional gastrointestinal symptoms over the last 2 months. We adapted the questionnaire and evaluated symptoms over a period of 4 weeks. Children completed the questionnaire themselves if they were aged 13–17 years, but parents completed the questionnaire if their child was aged 4–12 years. In addition, parents answered the question “Did your child use laxatives in the past four weeks?” (yes or no). If one or more responses were missing for the primary outcome measure, we contacted the child or parent by telephone to obtain an answer.

#### Measurement of secondary outcomes

Disease-specific quality of life was measured with the Defecation Disorder List (DDL), [17, 18] adapted to include only the emotional and social functioning subdomains. The constipation-related and treatment/intervention subdomains were omitted because it has previously been demonstrated that these have low internal consistency and potentially low validity when used to measure disease-specific quality of life [17, 18]. Health status was measured with the EuroQol-5-dimensions-youth (EQ-5D-Y) [19]. Proxy report versions of the DDL and EQ5D-Y questionnaires were completed by parents, and children aged ≥8 years also completed child self-reports. The global perceived treatment effect of patients (GPE) was scored by parents and measured with a 9-point Likert-type scale (very much, much, reasonable, and slightly improved; no change; slightly, reasonable, much, and very much worse). When parents reported that the symptoms of their child were improved very much or much we defined the treatment as successful.

Healthcare consumption related to FC, such as GP or pediatrician visits, drug treatment, and parental productivity loss, were measured with versions of the Institute of Medical Technology Assessment Medical Consumption Questionnaire (iMTA-MCQ) and the Productivity Costs Questionnaire (iMTA-PCQ), respectively, adjusted for FC [20, 21]. Both cost questionnaires were completed by parents only.

If questionnaires were not returned, participants were sent a reminder e-mail after 2 weeks and received a reminder telephone call after 3 weeks.

### Sample size

Sample size estimates were based on a systematic literature review showing that after 6 to 12 months of conventional treatment, 50% of the children were free of symptoms without using laxatives [22]. Physiotherapy in one study has been shown to improve outcomes by 30% compared with conventional treatment alone in children with FC referred to pediatric specialist care [14]. However, that study may have overestimated the magnitude of effect because it was small and underpowered [23]. Therefore, we used a more conservative estimate of the difference in treatment success (25%) between the intervention and control group. The sample size was calculated with expected treatment success rates after 6–12 months of 50 and 75% in the conventional and intervention groups, respectively [14, 22]. Given an expected loss to follow-up of 10%, we estimated a total sample size of 128 children (alpha 0.05, power 0.80).

### Statistical analyses

We will use appropriate descriptive statistics to describe patient characteristics, baseline questionnaire scores, and the proportions of successfully treated children at 4 and 8 months in the intervention and control groups.

We will use multilevel analyses to investigate the longitudinal relationship between the intervention group (physiotherapy plus conventional treatment) and the control group (conventional treatment) with respect to the primary and secondary outcome variables. The applied levels will be repeated measures (that is, time), and patient. We will base our analyses on intention to treat (ITT). The ITT population will consist of all patients who have given informed consent and have been randomly allocated to one of the two treatments, irrespective of whether they received the allocated treatment or not. An additional secondary per protocol analysis (PP) will be conducted for the outcome variable. The PP population will consist of all children randomized in the intervention group receiving at least one physiotherapy session and all children in the control group that had no physiotherapy. Finally, in a sensitivity analysis we will evaluate whether the effect of the intervention is different for children with and without chronic symptoms.

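### The multilevel model has levels for time and patient only; if outcomes correlate within physiotherapist, its standard error for the treatment effect will be too small, by an amount the protocol does not let one determine

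*Protocol article*

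**What the plan says.** The Statistical analyses section of the protocol article compares the arms by multilevel analysis "with respect to the primary and secondary outcome variables", by intention to treat, and then spells out the hierarchy: "The applied levels will be repeated measures (that is, time), and patient". No physiotherapist level is named.

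The Intervention group section describes delivery: "Physiotherapy consisted of a maximum of nine half-hour sessions carried out by specialist physiotherapists". The therapist has discretion over content ("The physiotherapist tailored the treatment program to the individual patient") and over duration, since treatment "ended if the physiotherapist considered that treatment was successful or that no more improvement was expected". The same section describes features that standardise care: a structured programme with six goals that was "approved by all participating specialist physiotherapists before the study", and a common record ("For each patient and session, the physiotherapists recorded on a structured form the treatment options used to reach the six goals"). The Control group section assigns no physiotherapist.

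The Sample size section plans 128 children for 50% versus 75% success, alpha 0.05, power 0.80 and 10% loss to follow-up. The article does not give the number of physiotherapists, their caseloads or an ICC, and mentions no design effect.

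**The concern.** Allocation is by individual child, but from the first session onward intervention children share therapists. A therapist who is more effective, or who ends treatment earlier or later than colleagues, shifts the outcomes of all his or her patients together. Controls have no counterpart to this, so the extra variance sits in one arm. A patient-level random effect does not capture it: it links the 4- and 8-month measurements of one child, but still treats different children as independent.

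At stake are the confidence interval and p-value of the primary comparison. With positive correlation and more than one child per therapist, the interval would be too narrow and the test would reject too often. Because the section states the levels, an analysis that follows it would carry the omission forward.

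**Working it through.** **1. Reproduce the planned sample size.** Inputs from the Sample size section: p1 = 0.50, p2 = 0.75, alpha 0.05 (two-sided assumed), power 0.80. With pooled variance under the null and no continuity correction:

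n = [1.96·√(2·0.625·0.375) + 0.8416·√(0.25 + 0.1875)]² / 0.25² = [1.342 + 0.557]² / 0.0625 ≈ 57.7, so 58 per arm and 116 in total.

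116 × 1.10 = 127.6, rounded to 128. The stated figure reproduces as a calculation for independent patients, with no allowance for clustering.

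**2. Set up the one-arm design effect.** Let m be children per physiotherapist and ICC the within-therapist correlation. Neither is in the documents; both are assumed.

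- Intervention arm: DEFF = 1 + (m − 1)·ICC. Control arm: 1.
- True SE / model SE, equal arm variances under the null: R = √[(1 + DEFF)/2].
- Understatement of the model SE: 1 − 1/R.
- Actual type I error at nominal 5%: 2·[1 − Φ(1.96/R)].
- Power of a valid analysis, unpooled: Φ(0.25/√(0.25/n + 0.1875·DEFF/n) − 1.96).
- Power, pooled: Φ([0.25 − 1.96·√(0.234375·(1 + DEFF)/n)] / √(0.25/n + 0.1875·DEFF/n)), where 0.234375 = 0.625·0.375.

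For n: 134 children were included; less 10% gives 120.6, or about 60 per arm.

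**3. Results at n = 60 per arm.**

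| m | ICC | DEFF | R | Model SE understated by | Type I error | Power, unpooled | Power, pooled |
|---|---|---|---|---|---|---|---|
| any | 0 | 1.00 | 1.000 | 0% | 5.0% | 0.83 | 0.82 |
| 3 | 0.02 | 1.04 | 1.010 | 1.0% | 5.2% | 0.83 | 0.81 |
| 5 | 0.05 | 1.20 | 1.049 | 4.7% | 6.2% | 0.80 | 0.78 |
| 10 | 0.05 | 1.45 | 1.107 | 9.6% | 7.7% | 0.76 | 0.73 |
| 10 | 0.10 | 1.90 | 1.204 | 17% | 10.4% | 0.70 | 0.66 |

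Example, bottom row: DEFF = 1 + 9 × 0.10 = 1.90; R = √1.45 = 1.204; 1 − 1/1.204 = 0.17; 1.96/1.204 = 1.628, giving 10.4%. Unpooled power: 0.25/√(0.60625/60) − 1.96 = 0.527, and Φ(0.527) = 0.70.

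**4. Limits of the calculation.** These are normal approximations for a difference in proportions at one time point, not for the two-visit multilevel model. They show direction and order of magnitude. Caseloads of 3 to 10 among 60 treated children would mean about 20 down to 6 therapists, so the larger effects go with few clusters.

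**The case against.** **Correlation within therapist is not shown.** Tailoring is to the patient, which in itself is variation between children and not similarity among those who share a therapist. Common goals, a jointly approved programme, master's-level training, a cap on sessions and the exclusion of biofeedback and electrotherapy should all reduce differences between therapists. Recruitment from 93 practices and 5 outpatient departments is compatible with small caseloads. This stands as to size: the ICC may be small. It does not make the ICC zero, because each therapist still shapes content and decides when treatment ends.

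**An article leaves detail to the analysis plan.** This holds for supplementary analyses, which the section does not exclude. It does not hold for the main model, whose levels are stated.

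**Therapists may be treated as fixed.** After individual randomisation, an analysis confined to the participating therapists is defensible. But the Background states an aim about physiotherapy for children in primary care, which reaches beyond those therapists.

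**A simple remedy would be flawed.** The per-protocol definition allows for intervention children with no session and for controls who obtain physiotherapy, so cluster membership needs a rule. An uncorrected cluster-robust variance is itself anti-conservative with few clusters. The session forms are described as recording treatment options; that they identify the therapist is an inference. All three points stand, and the fix takes account of them.

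**Conclusion.** The point holds conditionally. The stated two-level model ignores partial nesting, and its standard error for the treatment effect will be too small if the within-therapist ICC is above zero and therapists treat more than one child. Over the assumed caseloads (3 to 10) and ICCs (0.02 to 0.10), the true standard error is about 1% to 20% larger than the model's, which is an understatement of about 1% to 17%.

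A reader might infer that the standard errors are certainly too small, or that the trial is underpowered. The documents support neither: they give no caseload or ICC, nothing changes at ICC = 0 or m = 1, and the low end costs under one percentage point of unpooled power (0.833 to 0.827). Nor does the same one-arm argument extend to clustering by practice or physician, because children were randomised individually across both arms.

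The analysis should still be amended: the choice bears on the primary inference, its effect could be material, and it can be corrected by wording.

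**What to change.** Add to the Statistical analyses section a partially nested analysis of the primary outcome, with a physiotherapist random effect in the intervention arm only. Make it the main model or, at the least, a pre-specified sensitivity analysis.

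- Keep children in their randomised arm. Treat controls, and intervention children who never attended, as singletons.
- If there are few physiotherapists, use a small-sample correction and do not rely on an uncorrected cluster-robust variance.
- First confirm that the treating physiotherapist can be identified from the session forms.
- Report the number of physiotherapists, their caseloads and the estimated ICC.

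The cost is a change of analysis wording and, if the identifier can be recovered, no new data from the children. The downside is somewhat wider intervals and possible convergence problems with few therapists. If the estimated ICC is near zero, the two-level result stands and is better supported.

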## Discussion

Although two small clinical trials have shown that physiotherapy for FC could be a promising treatment for children in specialist care, [13, 14] we are not aware of any trial evaluating its effectiveness in primary care where most children with FC are diagnosed and treated [25]. The aim of physiotherapy is to improve the coordination between the abdominal and pelvic floor musculature during bowel movement [9]. The strength of physiotherapy is that physical exercises are combined with cognitive and behavioral elements, such as education and toilet training [26]. Treatment guidelines recommend that these cognitive and behavioral elements be discussed by doctors during a consultation [2, 3]. However, this might be problematic because GPs focus on symptomatic relief of symptoms. In addition, the consultation time is only 10 min in primary care, which limits the time for proper education, and advices on toilet training.

Initially, we had aimed to assess physiotherapy in children with recent-onset FC, for two main reasons. First, we assume that the long-term prognosis could be more improved if children receive treatment early in the disease process [4]. Second, we think that duration of symptoms and of treatments would be more homogenous in children with recent onset of symptoms. However, we discovered that parents and children could not be motivated for a time-intensive therapy like physiotherapy for symptoms they considered to be temporary and mild. Our subsequent comparison of participants and non-participants confirmed that children were more inclined to participate if they had longer symptom durations and regular laxative use. Therefore, our study will generate results on the effects of physiotherapy for children with more advanced FC than we had originally planned. Specifically, we expect our results to concern those cases where the child or parent have experienced conventional primary care treatment to be insufficient.

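### The secondary per-protocol set selects on a different post-randomisation event in each arm and is open to selection bias; the ITT result is not affected

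*Protocol article*

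**What the plan says.** In the protocol article, Statistical analyses, the main analysis is ITT: every consented and randomised child counts, "irrespective of whether they received the allocated treatment or not". The section then adds: "An additional secondary per protocol analysis (PP) will be conducted for the outcome variable". That set is made up of "all children randomized in the intervention group receiving at least one physiotherapy session and all children in the control group that had no physiotherapy".

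Four other places bear on who falls outside the set:

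- Control group section: "No restrictions or recommendations were given to the physicians regarding treatment". The next sentence names education, diet, toilet training and laxatives as components of care. Physiotherapy is neither named nor barred.
- Intervention group section: "Physiotherapy consisted of a maximum of nine half-hour sessions carried out by specialist physiotherapists". The course stops early when the therapist judges it successful or expects no further gain.
- Randomization and blinding: families, physicians and therapists know the allocation.
- Discussion: "we expect our results to concern those cases where the child or parent have experienced conventional primary care treatment to be insufficient".

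**The concern.** Randomisation makes the arms comparable only if children are kept in them regardless of what happens later. Here an intervention child leaves the set by never starting physiotherapy, and a control child leaves by obtaining it. These are different decisions, probably made by different kinds of family.

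On the control side, the families are unblinded, many already found usual care insufficient, and nothing in the text bars referral. A control child who obtains physiotherapy may well be one who is doing badly. Removing such children raises the success rate of the controls who remain. On the intervention side, a child may fail to start because symptoms are mild or because the family is disengaged, and these reasons pull in opposite directions.

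At stake is the one analysis that speaks to the effect of receiving physiotherapy, as opposed to being allocated to it. If it is selected, it cannot answer that question, and a gap between it and the ITT result cannot be interpreted.

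**Working it through.** **Inputs from the documents.** Success is 50% with conventional treatment and 75% with added physiotherapy (Sample size). Allocation is 1:1 and 134 children were included, so about 67 per arm. The plan gives no figure for the per-protocol set. The rates used here are those behind its sample size, which reproduces: a two-sided, pooled-variance calculation gives 58 per arm, 116 in total, and 116 × 1.10 = 127.6, or 128 (116/0.90 gives 129).

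**Assumed inputs.** The documents give no crossover or non-starter rate and do not link either to prognosis. Let c be the share of controls who obtain physiotherapy, and f the success rate those children would have had without it. At c = 10%, about 0.10 × 67 = 6.7, or 7 children, are involved.

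**Control side.** Per-protocol control success = (0.50 − c·f)/(1 − c). The shift in the difference is 0.50 minus that rate.

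For c = 10%:
- f = 50%: (0.50 − 0.05)/0.90 = 50.0%; shift 0.
- f = 25%: (0.50 − 0.025)/0.90 = 52.8%; shift −2.8 points.
- f = 0%: 0.50/0.90 = 55.6%; shift −5.6 points.

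| c | f = 50% | f = 25% | f = 0% |
|---|---|---|---|
| 5% | 0 | −1.3 | −2.6 |
| 10% | 0 | −2.8 | −5.6 |
| 20% | 0 | −6.25 | −12.5 |

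A planned 25-point effect would thus read as 25.0, 22.2 or 19.4 points at c = 10%. With no true effect, c = 10% and f = 0%, the per-protocol difference would be −5.6 points where ITT gives 0.

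**Intervention side.** Let d be the share who never start and s their success rate. With a 50% rate in the arm, the remaining rate is (0.50 − d·s)/(1 − d). At d = 10%:
- s = 25%: 0.475/0.90 = 52.8%; shift +2.8.
- s = 75%: 0.425/0.90 = 47.2%; shift −2.8.
- s = 100%: 0.40/0.90 = 44.4%; shift −5.6.

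**Comparison with a randomisation-based estimate.** The complier effect is the ITT difference divided by the difference between arms in the share receiving at least one session. Take c = 10%, f = 0% and every intervention child starting, so the divisor is 1 − 0.10 = 0.90.

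| Success of crossovers after physiotherapy | ITT | Per protocol | Complier effect |
|---|---|---|---|
| 0% | 75 − 50 = 25.0 | 19.4 | 25.0/0.90 = 27.8 |
| 50% | 75 − 55 = 20.0 | 19.4 | 20.0/0.90 = 22.2 |

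The second row shows what goes wrong. Children who would obtain physiotherapy under either allocation exist in both arms, but the per-protocol rule removes them from the control arm only. It compares 75% (the whole intervention arm) with 55.6% (control compliers only). If the same children could be taken out of the intervention arm, its compliers would succeed at (0.75 − 0.10 × 0.50)/0.90 = 77.8%, and 77.8 − 55.6 = 22.2, which is the complier effect.

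**The case against.** Much of the opposing case stands.

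- **Status.** The analysis is explicitly additional to ITT. A reader might infer that the trial's main result is compromised or will be replaced. The documents do not support that: the ITT set is correctly defined and untouched by this rule.
- **No rate.** A reader might also infer that the per-protocol estimate is biased as a matter of fact. That needs exclusions that occur and are related to outcome, and the documents show neither. The listed components of control care do not include physiotherapy, so crossover may be rare. The column with f = 0% is the extreme.
- **Direction.** Removing failing controls shrinks the apparent benefit, so this mechanism would not create a false positive. The intervention side has no predictable sign.
- **ITT is not a fixed yardstick.** If crossovers benefit, ITT is diluted too. In the second scenario above, per protocol and ITT differ by only 0.6 points (19.4 against 20.0).
- **The alternative has its own weak point.** A complier effect assumes that allocation affects the outcome only through receipt of physiotherapy (the exclusion restriction). With unblinded families and outcomes reported by parent or child, that can be questioned. It is also a different estimand: in the first scenario it is 27.8, not 25.

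Labelling and tabulation could be in an analysis plan that is not shown, so their absence here is no fault. The membership rule itself, however, is fixed in the article. A debatable assumption that is stated openly is also no reason to prefer a comparison that gives up the protection of randomisation.

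**Conclusion.** The point holds as a moderate weakness of a secondary analysis. The per-protocol set is conditioned on different post-randomisation events by arm and is open to selection bias. At an assumed 10% control crossover, the shift runs from 0 points (crossover unrelated to prognosis) through −2.8 (f = 25%) to −5.6 points (all crossovers failing). It is zero if nobody crosses over. Exclusion of non-starters adds a shift of either sign, from +2.8 to −5.6 points in the cases worked. These sizes rest on the planning rates and on assumed crossover, non-starter and prognosis figures. The conclusion that ITT is unaffected rests on no assumption beyond the plan's own definition.

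**What to change.** Keep inference on ITT. For the effect of receiving physiotherapy, specify a complier-average causal effect in all randomised children:

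- Use randomised allocation as the instrument for at least one physiotherapy session. This is the plan's own threshold, applied identically in both arms.
- Adjust for the stratification factor, age group (4–8 or 9–17 years). The section names no other covariates.
- Handle missing outcomes as in the ITT analysis.

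If the per-protocol table is kept, label it descriptive and show exclusions by arm with reasons.

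**Cost.** This is a change of wording, and the analysis is described as still to come. Receipt must be known in both arms, but the per-protocol rule already requires that.

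**Downsides to state.**
- The interval is wider: at 10% crossover with all intervention children starting, roughly 1/0.90 = 1.11 times the ITT width, treating the receipt rates as known.
- The estimand is the effect in compliers.
- The estimate relies on the exclusion restriction, and on there being no defiers (children who would receive physiotherapy only if allocated to control), in an unblinded trial.
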